### Blinding

Due to the nature of the intervention, neither the participants nor the research assistant can be blinded to the intervention. Additionally, the collection of the primary and explorative outcomes will not be blinded. At study completion, a researcher not involved in the research project will extract data from REDCap into two separate files where group allocation will be coded as A and B to ensure blinding during the period of data analyses, interpretation, and drafting of the first manuscript. The blinding will be unmasked once the conclusion has been written.

## Discussion

Emerging research suggests that specialized apps targeting self-injurious behaviour, which can be used anonymously and in private, have the potential to help people with NSSI [23, 24]. However, randomized controlled trials confirming the effectiveness of these apps in different settings are warranted [23, 24].

The ZSH intervention has several strengths. First, by involving stakeholders and people with lived experiences in the development of the app, the app’s content is likely to be relevant to the target group. Second, by having a focus on minimizing harm, the app might be more appealing and acceptable to a broader group of users. Third, by listing the app under an undisclosed name, contamination of the trial’s data will be limited.

Potential limitations should be noted. Firstly, although the app was developed in collaboration with individuals with lived experiences, it may not address the needs of everyone engaging in NSSI. Individuals with NSSI are characterized by broad age spans, diagnoses, severity and versatility of NSSI, and co-morbidities. Although it might be beneficial to also collect feedback and insights from next of kin and professionals, this was beyond the scope of this intervention.

Secondly, it is important to acknowledge that the use of the app might maintain or possibly worsen NSSI. To investigate this potential limitation, the first 20 participants will be asked after 3 months about whether they have had any negative experiences or side effects of the app. Other potential limitations could be linked to how users learn how to use the app, which for some participants can be difficult and overwhelming. It might result in some participants using the app only a few times or not at all. Even though a thorough onboarding process is carried out, more continuous and structured support might improve the usage of the app. Another way of combining a more structured support with technology could also have been by using for instance automatically collected smartphone sensor data, which is not included in this trial. In general, having a self-help app as an intervention can be challenging since technological development is an on-going process. Some of the app features designed to be user-friendly can potentially become outdated during the trial. Once the trial is started, the app cannot undergo significant changes, and this could limit the possibility of continuously ensuring the relevance of the app and its design.

Thirdly, the broad recruitment strategy might imply that participants using a range of mental health services will be included, which potentially could affect the treatment outcome. Persistent self-harm behaviours and more severe underlying psychopathology could affect the effect of the app. By collecting information on the received treatment, we can adjust for this in the analysis. However, there might be a difference in how the general experience of the app is, depending on the knowledge level of NSSI and the degree and duration of the NSSI. The broad variation of participants, which includes both individuals with milder symptoms of NSSI and more severe and chronic NSSI, can make it difficult to distinguish a potential difference in maybe the usage of the app, how relevant the app is perceived and the outcome of the app. Also, specialized treatment for NSSI is an exclusion criterion which can furthermore make the recruitment more difficult.

The questionnaires in the trial cover different topics such as NSSI, suicidal ideation, depressive symptoms, and self-esteem which for some of the participants can be difficult to reflect on and quantify. Avoidance of these topics might occur and make it more difficult to get the questionnaires answered, especially since it is self-administered questionnaires. The questionnaires are sent out three times with a 3-month interval and that can also be an obstacle since it requires time and effort which can lead to participant dropout.

Finally, neither the participants nor the research assistant will be blinded to the assignment of treatment condition due to the nature of the intervention. However, the research assistant will remain blinded during the analysis and drafting of the manuscript.

A worsening of the condition of a participant may occur during the trial. To ensure the participants know where to seek help, the research assistant will inform all participants in the enrollment process about relevant support options. As part of the onboarding process, the intervention group will be offered an introduction by phone on how the app can be used as a safety plan and important phone numbers to emergency services are pre-installed in the app, etc. The research assistant will be available to answer questions regarding the app or the questionnaires and give technical support throughout the trial.

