**Fig. 1 Fig1:**
[figure not shown]
Flow diagram of the Zero Self-Harm intervention

**Table 1 Tab1:** World Health Organization Trial Registration Data set

Data category	Information
Primary registry and trial identifying number	ClinicalTrials.gov NCT04463654
Date of registration in primary registry	07/07/2020
Secondary identifying number	Trygfonden 127390, The Regional Ethics Committee in the Capital Region of Denmark H 19024725
Source(s) of monetary or material support	TrygFonden reference number: 127390
Primary sponsor	[name], Psychiatric Centre North Zealand; Denmark
Contact for public queries	KA: [contact]
Contacts for scientific queries	KA: [contact]
Public title	Zero Self-Harm - a Mobile Phone Application to Reduce Non-suicidal Self-injury
Scientific title	Zero Self-Harm - a Mobile Phone Application to Reduce Non-suicidal Self-injury: A Randomized Clinical Superiority Trial
Country of recruitment	Denmark
Health condition(s) or problem(s) studied	Self-injurious behavior
Intervention(s)	Device: Zero Self-Harm app, safety plan app for smartphones
Key inclusion and exclusion criteria	Ages eligible for study: ≥ 18 years; sexes eligible for study: both Inclusion Criteria: Engagement in two or more episodes of NSSI in the past month, have a smartphone (IPhone or Android phone), fluent in Danish, skills sufficient to enable use of the Zero Self-Harm app, provide an informed written consent. Exclusion Criteria: Lack of informed consent, further planned specialized treatment focused on NSSI.
Study type	Allocation: Randomized Interventional Model: Parallel Assignment Masking: Single (Outcomes Assessor) Primary Purpose: Prevention
Date of first enrolment	October 15, 2020
Target sample size	280
Recruitment status	Not recruiting
Primary outcome(s)	Number of self-harm episodes: Deliberate Self Harm Inventory [Time Frame: 6 months]
Key secondary outcome(s)	Suicide ideation: Becks Suicide Ideation Scale [Time Frame: 6 months] Depression: Major Depression Inventory (MDI) [Time Frame: 6 months] Well-being: WHO Well-being Index [Time Frame: 6 months] Self-esteem: Rosenberg's Self-Esteem scale [Time Frame: 6 months]

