### Enrollment and randomization

Interested individuals will be encouraged to contact the research assistant through phone or e-mail. They will be provided with verbal and written information about the study, in which it is emphasized that participation is voluntary and that they may withdraw their consent at any time. They may take time to consider or discuss the participation with a next of kin before deciding whether to enrol in the study. During the enrollment phase, the potential participants will be interviewed by using the Mini-International Neuropsychiatric Interview (MINI) [32] and informed consent will be collected via an e-mail from REDCap [33] to the secure digital platform e-Boks where Danish citizens receive verified information [34]. The research assistant will make sure to get the informed consent in the enrollment phase. The participant information materials and informed consent form are available from the corresponding author.

After enrollment, participants will be administered the baseline questionnaires. Subsequently, they will be randomly assigned to either the intervention or the control group in a 1:1 allocation, using REDCap’s feature for a computer-generated sequence randomization. The randomization will be stratified by sex and number of NSSI episodes, as measured at baseline by the Deliberate Self Harm Inventory, to avoid overrepresentation of participants with a high number of NSSI episodes in one group. This stratification will be also facilitated through REDCap. The research assistant will generate the allocation sequence in REDCap after enrolling the participant and inform the participant which group, they are assigned to.

As part of the enrollment process, all participants will be informed that they can contact the research assistant in case of questions or technical problems. Participants will also receive information on where they can seek help if needed, for instance through helplines and the emergency services, such as 1318 and 112.

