### Data collection

The participants will be administered questionnaires at baseline (*T*_0_) and at two follow-up time point (*T*_1_=3 months and *T*_2_= 6 months). At baseline, the participants will undergo the MINI interview and there will be socio-demographic questions, including age, gender, and use of psychiatric services. The MINI is administered by the research assistant. All other questions will be self-administered and sent to the participant by e-mail at baseline and follow-up. All the participants will be allocated an individual trial identification number and all data will be collected in REDCap in a central computer storage under Mental Health Services in the Capital Region of Denmark.

To promote participant retention, robot-generated reminders will be sent out 1 week after the dissemination of questionnaires. If participants have not completed the questionnaire a week after the reminder was sent out, the research assistant will contact the participant and encourage them to answer the questionnaires and assist with any technical problems. All the participants will receive a minor gift card to a coffee shop once the questionnaire is completed. If a participant wishes to discontinue their participation, their data will be deleted. Still, the number of discontinuations will be reported in the Consort flow diagram. The Project Management Group is planned to meet on a weekly basis and the Trial Steering Committee will meet approximately every third month to review trial conduct and progress. The Ethical Committee and the independent Data Monitoring can review trial conduct throughout the whole trial period.

To secure data confidentiality, data on participants will be stored in a logged and closed computer drive in the Mental Health Services in Capital Region of Denmark. It will be stored until 5 years after the trial has finished. Afterwards, data will be permanently deleted.

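### Table 1 lists a masked outcomes assessor, but the Blinding section leaves collection of a self-reported primary outcome unblinded; only the data files are coded

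*Protocol article*

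**What the plan says.** In Table 1 (World Health Organization Trial Registration Data set), the study-type row gives "Masking: Single (Outcomes Assessor".

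The Blinding section states that "neither the participants nor the research assistant can be blinded to the intervention" and adds that "the collection of the primary and explorative outcomes will not be blinded". The masking it does provide comes after data collection: "group allocation will be coded as A and B to ensure blinding during the period of data analyses, interpretation, and drafting of the first manuscript".

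What the assistant knows is shown in the section on enrollment and randomization: "The research assistant will generate the allocation sequence in REDCap after enrolling the participant and inform the participant which group, they are assigned to". The Intervention section has the same assistant invite the app arm, and only that arm, to a phone call one week after inclusion. The Data collection section says that everything except the MINI interview is self-administered and e-mailed to the participant. For late questionnaires, "the research assistant will contact the participant and encourage them to answer the questionnaires and assist with any technical problems".

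The Discussion repeats, among the limitations, that participants and assistant are not blinded. It then says that the assistant stays blinded while the data are analysed and the manuscript is drafted. On the assistant's continuing role it says: "The research assistant will be available to answer questions regarding the app or the questionnaires and give technical support throughout the trial".

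**The concern.** A masking entry is a claim about how the outcome was measured. Readers of the trial report, and anyone who rates its risk of bias, will take a masked outcomes assessor to mean that the person who produced the outcome value did not know the allocation. Here that value is a participant's own count of self-injury episodes over the past month, given by someone who knows whether they have the app or are waiting for it. Expectation or disappointment can move such a count in either arm, and analysts who see only A and B cannot undo it.

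The statement that the assistant stays blinded raises the same difficulty: a person who has announced the allocations cannot become unaware of them later.

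A lesser point concerns the assistant's contact with participants. The Discussion lists questions about the questionnaires separately from technical support, so content questions fall within the role. They are foreseeable, since the Discussion itself expects some participants to find topics including NSSI hard to quantify, and the DSHI asks for counts across 17 methods. Unscripted answers from someone who knows the allocation are an avoidable route for bias.

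**Working it through.** **1. The masking statements side by side (protocol article).**

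- Participants: not blinded (Blinding; repeated in the Discussion).
- Research assistant: not blinded, and tells each participant the allocation (Blinding; Enrollment and randomization).
- Outcome collection, primary and explorative: not blinded (Blinding).
- Who produces the primary outcome value: the participant, by self-administered DSHI (Outcomes; Data collection).
- Analysis, interpretation and drafting: arms coded A and B (Blinding).
- Table 1: outcomes assessor masked.

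The first four lines leave nobody who could be a masked assessor. The fifth masks the analysts, who work on values already reported. The Table 1 entry therefore has no counterpart in the described conduct.

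**2. The statement on the assistant.** Staying blinded requires having been blinded. The assistant knows the allocations from randomization onwards. What can be withheld is which coded file belongs to which arm, and that is a property of the files.

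**3. The plan's own figure.** The sample size is not in dispute and reproduces. Inputs from the Sample size section: difference 3.5, SD 9, power 90%, alpha 0.05. The Statistical analysis section makes the tests two-tailed, and allocation is 1:1.

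- Normal approximation: n = 2 × (1.960 + 1.282)² × 9² / 3.5² = 138.9, so 139 per arm.
- Two-sample t-test: 139.9, so 140 per arm and 280 in total, as stated. Power at 140 per arm is 0.900.

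**4. Can the bias be sized?** Not from the documents, which give no figure for differential reporting. An illustration on assumed values shows only the sensitivity of the test. The standard error of the difference is 9 × √(2/140) = 1.08 episodes, with complete data. With no true effect and an assumed shift b between arms in reported counts, the two-sided rejection rate is Φ(b/1.08 − 1.96) + Φ(−b/1.08 − 1.96):

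- b = 0.5: about 7.5%
- b = 1.0: about 15%
- b = 1.5: about 29%
- b = 2.0: about 46%

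Every b is an assumption, and nothing in the documents favours one over another. The contradiction in step 1 does not depend on this step.

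**The case against.** The strongest defence is that the Blinding section, where a reader looks for this, is candid: it says without qualification that outcome collection is open, and the Discussion lists the lack of blinding as a limitation. On that view only one cell of a registration table is off, perhaps because the coded analysis was entered under the nearest available label. Much of this stands. A reader might infer that the plan denies the bias. It does not; it discloses the lack of blinding, although it does not name reporting bias as the consequence. The cell is still wrong, because analysing coded files is not assessing outcomes.

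A reader might also infer that the two arms are chased differently for missing questionnaires. The Data collection section does not support that: one automated reminder and one later contact apply to all participants. Nor does any section say that the assistant scores the DSHI or advises on what to count. The documents show that content questions may be answered, not how.

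Three further objections stand. Written replies and contact logs are operating detail that an article may leave to the full protocol, so their absence is no fault. Scripting the assistant would leave the main source of bias, the unblinded participant compared with a waitlist, in place. And the Trial status section gives enrollment until September 2023 and the last questionnaire on 22 February 2024, so a procedural change reaches few contacts. None of these removes the need to correct what the article states about masking.

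**Conclusion.** The point holds as a contradiction about masking. Table 1 gives the trial a masked outcomes assessor, which the Blinding and Data collection sections rule out, and the Discussion's statement that the assistant stays blinded conflicts with that person's knowledge of the allocations. This rests on the text alone and needs no assumption. The practical effect is on what the trial may claim: coded analysis, yes; masked outcome assessment, no. The sample size and the other planned figures are unaffected.

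The self-reported primary outcome is open to reporting bias by design. Its size and direction cannot be derived from the documents, so no figure should be attached to it. The assistant's permission to answer questionnaire questions is a secondary route that merits a cheap safeguard; it is not evidence that counts were influenced.

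**What to change.** 1. **Table 1.** Change the masking entry to open label: participants, research assistant and outcome collection not masked; data files coded A and B for analysis, interpretation and drafting. Change the registry entry too if it reads the same. This costs a text edit and the loss of a more favourable label, and it can be done at any stage.
2. **Discussion.** Replace the statement that the assistant stays blinded with one saying that only the data files are coded. This is a text edit.
3. **Interpretation.** State in the limitations and in the trial report that the primary outcome is self-reported by unblinded participants against a waitlist, and read the effect estimate as open to reporting bias. The cost is a more cautious conclusion.
4. **Contacts still outstanding.** Have the assistant answer questions on questionnaire content only from one written reply sheet, used identically in both arms; technical help can continue as planned. This costs one short document. The downsides are less individual help with difficult items, and late participants handled differently from earlier ones. It cannot protect data already collected.

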### Trial status

The trial began to recruit participants in October 2020 and the recruitment and enrollment have continued until September 2023. The last questionnaire (the 6-month follow-up) will be sent to the last participant on 22 February 2024. Due to delays caused by the COVID-19 pandemic, change of research staff members and maternity leave, it has not been possible to submit this study protocol earlier. The protocol version number is 1.2, dated 30 July 2020.

## Data Availability

Following the Consort guidelines, we will publish positive, neutral, and negatives findings. The dissemination plan for the trial is regardless of results it will sought to be published in scientific journals and we will participate in national and internationals congresses. Any data required to support the protocol can be supplied on request. The dataset is available from the corresponding author on reasonable request.

## Abbreviations

NSSI: Non-suicidal self-injury
app: Mobile phone application
ZSH: Zero self-harm
MINI: Mini-International Neuropsychiatric Interview
